# A Phase 2 Study of R-(-)-gossypol (Ascenta's AT-101) in Recurrent Glioblastoma Multiforme

NABTT #: 0702

NCI #: NABTT 0702

Principal Investigator: [name]

|                                                        |                              |  |                               |
|--------------------------------------------------------|------------------------------|--|-------------------------------|
|                                                        | Blood bilirubin increased    |  |                               |
|                                                        | Cardiac troponin I increased |  |                               |
|                                                        | Cardiac troponin T increased |  |                               |
|                                                        | Creatinine increased         |  |                               |
|                                                        | Weight loss                  |  | Weight loss            |
|                                                        | White blood cell decreased   |  |                               |
| METABOLISM AND NUTRITION DISORDERS              |                              |  |                               |
| Anorexia                                               |                              |  | Anorexia               |
|                                                        | Dehydration                  |  | Dehydration            |
|                                                        | Hypocalcemia                 |  |                               |
|                                                        | Hypokalemia                  |  | Hypokalemia            |
|                                                        | Hypomagnesemia               |  | Hypomagnesemia         |
| MUSCULOSKELETAL AND CONNECTIVE TISSUE DISORDERS |                              |  |                               |
|                                                        | Back pain                    |  |                               |
|                                                        | Pain in extremity            |  |                               |
| NERVOUS SYSTEM DISORDERS                        |                              |  |                               |
|                                                        | Dizziness                    |  | Dizziness              |
|                                                        | Dysgeusia                    |  | Dysgeusia              |
|                                                        | Headache                     |  |                               |
| PSYCHIATRIC DISORDERS                           |                              |  |                               |
|                                                        | Insomnia                     |  |                               |
|                                                        | Libido decreased             |  | Libido decreased       |
| REPRODUCTIVE SYSTEM AND BREAST DISORDERS        |                              |  |                               |
|                                                        | Azoospermia                  |  | Azoospermia            |
|                                                        | Irregular menstruation       |  | Irregular menstruation |
| RESPIRATORY, THORACIC AND MEDIASTINAL DISORDERS |                              |  |                               |
|                                                        | Cough                        |  |                               |
|                                                        | Dyspnea                      |  | Dyspnea                |
| SKIN AND SUBCUTANEOUS TISSUE DISORDERS          |                              |  |                               |
|                                                        | Dry skin                     |  | Dry skin               |
|                                                        | Pruritus                     |  |                               |
|                                                        | Rash maculo-papular          |  |                               |

 This table will be updated as the toxicity profile of the agent is revised. Updates will be distributed to all Principal Investigators at the time of revision. The current version can be obtained by contacting [[contact]](mailto:[contact]). Your name, the name of the investigator, the protocol and the agent should be included in the e-mail.

**Also reported on (R)-(-)-Gossypol acetic acid (AT-101) trials but with the relationship to (R)-(-)-Gossypol acetic acid (AT-101) still undetermined:**

**BLOOD AND LYMPHATIC SYSTEM DISORDERS** - Lymph node pain

**CARDIAC DISORDERS** - Myocardial infarction; Pericardial effusion; Sinus tachycardia

**EYE DISORDERS** - Blurred vision; Dry eye

**GASTROINTESTINAL DISORDERS** - Dysphagia; Flatulence; Hemorrhoids; Mucositis oral

**GENERAL DISORDERS AND ADMINISTRATION SITE CONDITIONS** - Chills; Edema face

**INFECTIONS AND INFESTATIONS** - Infections and infestations - Other (acute bacterial pancreatitis); Infections and infestations - Other (Opportunistic infection associated with  $\geq$  Grade 2 Lymphopenia)

**INJURY, POISONING AND PROCEDURAL COMPLICATIONS** - Bruising

**INVESTIGATIONS** - Neutrophil count decreased; Platelet count decreased

**METABOLISM AND NUTRITION DISORDERS** - Hyperglycemia; Hyperuricemia; Hyponatremia

**MUSCULOSKELETAL AND CONNECTIVE TISSUE DISORDERS** - Arthralgia; Bone pain; Myalgia

**NERVOUS SYSTEM DISORDERS** - Depressed level of consciousness; Olfactory nerve disorder

**PSYCHIATRIC DISORDERS** - Anxiety

## A Phase 2 Study of R-(-)-gossypol (Ascenta's AT-101) in Recurrent Glioblastoma Multiforme

NABTT #: 0702

NCI #: NABTT 0702

Principal Investigator: [name]

**RENAL AND URINARY DISORDERS** - Acute kidney injury; Hematuria; Proteinuria; Renal and urinary disorders - Other (urine odor abnormal)

**REPRODUCTIVE SYSTEM AND BREAST DISORDERS** - Testicular pain

**RESPIRATORY, THORACIC AND MEDIASTINAL DISORDERS** - Allergic rhinitis; Epistaxis; Pleural effusion; Pleuritic pain

**SKIN AND SUBCUTANEOUS TISSUE DISORDERS** - Alopecia

**VASCULAR DISORDERS** - Hot flashes; Thromboembolic event

**Note:** (R)-(-)-Gossypol acetic acid (AT-101) in combination with other agents could cause an exacerbation of any adverse event currently known to be caused by the other agent, or the combination may result in events never previously associated with either agent.

### **9.4 Expedited Adverse Event Reporting**

#### **Adverse Event Expedited Reporting System - AdEERS**

Expedited AE reporting for this study must use AdEERS (Adverse Event Expedited Reporting System), accessed via the CTEP home page (<http://ctep.cancer.gov>). The reporting procedures to be followed are presented in the “CTEP, NCI Guidelines: Adverse Event Reporting Requirements” which can be downloaded from the CTEP home page (<http://ctep.cancer.gov>). These requirements are briefly outlined in the table below (Section 9.4.1).

In the rare occurrence when Internet connectivity is disrupted, a 24-hour notification is to be made to CTEP by telephone at [contact]. An electronic report must be submitted immediately upon re-establishment of internet connection. Please note that all paper AdEERS forms have been removed from the CTEP website and can no longer be accepted.

**‘Expectedness’:** AEs can be ‘Unexpected’ or ‘Expected’ for expedited reporting purposes only. ‘Expected’ AEs (the ASAEL) are ***bold and italicized*** in the CAEPR.

### 9.4.1 Expedited Reporting Guidelines

AdEERS Reporting Requirements for Adverse Events that occur within 30 Days of the Last Dose of the Investigational Agent on Phase 2 and 3 Trials

| Phase 2 and 3 Trials                                                                                                                                                                                                                                                                                                                                                                                                                                                                                                                                                                                                                                                                                                                                                               |                         |                  |              |                                 |                                    |                               |                                  |                           |                           |
|------------------------------------------------------------------------------------------------------------------------------------------------------------------------------------------------------------------------------------------------------------------------------------------------------------------------------------------------------------------------------------------------------------------------------------------------------------------------------------------------------------------------------------------------------------------------------------------------------------------------------------------------------------------------------------------------------------------------------------------------------------------------------------|-------------------------|------------------|--------------|---------------------------------|------------------------------------|-------------------------------|----------------------------------|---------------------------|---------------------------|
|                                                                                                                                                                                                                                                                                                                                                                                                                                                                                                                                                                                                                                                                                                                                                                                    | Grade 1                 | Grade 2          | Grade 2      | Grade 3                         |                                    | Grade 3                       |                                  | Grades 4 & 5  | Grades 4 & 5  |
|                                                                                                                                                                                                                                                                                                                                                                                                                                                                                                                                                                                                                                                                                                                                                                                    | Unexpected and Expected | Unexpected       | Expected     | Unexpected with Hospitalization | Unexpected without Hospitalization | Expected with Hospitalization | Expected without Hospitalization | Unexpected                | Expected                  |
| Unrelated Unlikely                                                                                                                                                                                                                                                                                                                                                                                                                                                                                                                                                                                                                                                                                                                                                                 | Not Required            | Not Required     | Not Required | 10 Calendar Days                | Not Required                       | 10 Calendar Days              | Not Required                     | 10 Calendar Days          | 10 Calendar Days          |
| Possible Probable Definite                                                                                                                                                                                                                                                                                                                                                                                                                                                                                                                                                                                                                                                                                                                                                         | Not Required            | 10 Calendar Days | Not Required | 10 Calendar Days                | 10 Calendar Days                   | 10 Calendar Days              | Not Required                     | 24-Hour; 5 Calendar Days  | 10 Calendar Days          |
|  Adverse events with attribution of possible, probable, or definite that occur greater than 30 days after the last dose of treatment with an agent under a CTEP IND require reporting as follows:
AdEERS 24-hour notification followed by complete report within 5 calendar days for: 
 
Grade 4 and Grade 5 unexpected events
 
 AdEERS 10 calendar day report: 
 
Grade 3 unexpected events with hospitalization or prolongation of hospitalization
 
Grade 5 expected events
 
  Although an AdEERS 24-hour notification is not required for death clearly related to progressive disease, a full report is required as outlined in the table. |                         |                  |              |                                 |                                    |                               |                                  |                           |                           |
| December 15, 2004                                                                                                                                                                                                                                                                                                                                                                                                                                                                                                                                                                                                                                                                                                                                                                  |                         |                  |              |                                 |                                    |                               |                                  |                           |                           |

**Note:** All deaths on study require both routine and expedited reporting regardless of causality. Attribution to treatment or other cause should be provided.

- Expedited AE reporting timelines defined:
  - “24 hours; 5 calendar days” – The investigator must initially report the AE via AdEERS within 24 hours of learning of the event followed by a complete AdEERS report within 5 calendar days of the initial 24-hour report.
  - “10 calendar days” - A complete AdEERS report on the AE must be submitted within 10 calendar days of the investigator learning of the event.
- Any medical event equivalent to CTCAE grade 3, 4, or 5 that precipitates hospitalization (or prolongation of existing hospitalization) must be reported regardless of attribution and designation as expected or unexpected with the exception of any events identified as protocol-specific expedited adverse event reporting exclusions.
- Any event that results in persistent or significant disabilities/incapacities, congenital anomalies, or birth defects must be reported via AdEERS if the event occurs following treatment with an agent under a CTEP IND.
- Use the NCI protocol number and the protocol-specific patient ID assigned during trial registration on all reports.

#### 9.4.2 Exceptions to Expedited Reporting Guidelines

| CTCAE Category       | Adverse Event | Grade | Hospitalization/
Prolongation of
Hospitalization | Attribution | Comments |
|----------------------|---------------|-------|--------------------------------------------------------|-------------|----------|
| BLOOD/BONE
MARROW | Hemoglobin    | 2     | No                                                     | Possible    |          |
|                      | Leukoctyes    | 2-4   | No                                                     | Possible    |          |
|                      | Platelets     | 2     | No                                                     | Possible    |          |
| Gastrointestinal     | Diarrhea      | 3     | No                                                     | Possible    |          |
|                      | Nausea        | 3     | No                                                     | Possible    |          |
|                      | Vomiting      | 3     | No                                                     | Possible    |          |

#### 9.4.3 ABTC Reporting

Those Adverse Events described in Section 9.4.1 requiring immediate reporting (within 24 hours) to the NCI Investigational Drug Branch, CTEP will utilize the AdeERS 24-hour notification pathway accessible via web at <http://ctep.cancer.gov/reporting/adeers.html>.

Additionally a phone call must be made to:

**[name]**  
**ABTC Data Coordinator**  
**Office: [contact]**  
**[contact]**  
**[contact]**

In addition to the initial 24-hour report, all Adverse Events must be documented on the ABTC AE Form and using the AdeERS application. The AdeERS Form should be submitted to the ABTC Central Office and CTEP/NCI within 10 days of the event. Criteria for documenting the relationship to study drug and severity will be the same as those previously described.

**ABTC [contact]**

**These events also must be reported by the Investigator to the appropriate Institutional Review Board (IRB).**

Patients who are removed from study due to adverse events should be followed until the adverse event has resolved or stabilized. Copies of relevant documentation, such as laboratory reports, should be kept with the patient's study records.

## **9.5 Investigational Studies/Laboratory Correlates**

### **9.5.1 Tumor Tissue**

Tumor tissue will also be collected to analyze certain biomarkers. At the time of registration, prior to beginning treatment with AT-101 a tumor tissue form will need to be completed and signed by a pathologist. This form provides written documentation of the availability of tissue for this study and the pathologist's agreement to send it as described below.

Archived tumor tissue samples (tumor should be from the most recent tumor block available) will be collected, if available, for patients enrolled on this study. Investigators are to collect and ship one block or 15-20 slides of unstained, paraffin-embedded tissue. Tissue will be used for biomarker studies to determine intra-tumoral expression levels of relevant biomarkers, which may include, but are not limited to:

- Bcl-2 family protein expression (e.g., Bcl-2, Bcl-xL, Mcl-1, Bax, Bak, and BH3 domain for BH3 members only);
- MGMT gene methylation status;

Every effort will be made to collect tissue from additional surgeries the patient may have while on study.

### **9.5.2 Serum Biomarkers**

Serum will be collected from all patients for analysis of apoptotic protein levels (ex bcl-2) immediately (within 24 hours) before the first dose and after one week of therapy (any time during week 2 of cycle 1). Protein levels measured by ELISA will be correlated with clinical outcomes including overall survival and six month progression free survival.

Blood samples should be 10 ml collected in a standard non-additive collection tube (red top). After coagulation the sera should be collected and stored at -20°C until shipping. Specimens should be labeled with the date and time of collection and ABTC patient number. Samples should be shipped under dry ice to:

[name].  
UAB Department of Radiation Oncology  
[name]  
[name]  
[name]  
[contact] (voice)  
[contact] (fax)

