### Secondary Objectives

- 1) To assess and estimate the acute and late toxicities.
- 2) Tumor response rate.
- 3) To estimate 6-month progression free survival.
- 4) To explore associations of the clinical outcome (overall survival) among the changes of potential serum biomarkers, baseline tumor protein expression and gene methylation status.

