**We hypothesize the correlative biomarkers will predict overall survival and six month progression free survival.**

Although direct tissue analysis before and after treatment may provide the most specific biomarker predictive assays, such analyses are not likely to be accepted as conventional practice in brain tumor patients. Therefore, we propose to collect pathologic material from previous biopsy specimens from all patients whenever possible. This material will be archived for later analysis if the clinical data suggests subsets of patients have benefited from AT-101.

However, serum will be collected for analysis of apoptotic protein levels (ex bcl-2) immediately before the first dose and after one week of therapy. Protein levels measured by ELISA will be correlated with clinical outcomes including overall survival and six month progression free survival.

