### **11.3 Secondary Objectives**

1. To assess the acute and late toxicities associated with the treatment. The proportion of patients with serious or life threatening toxicities will be estimated along with 95% confidence intervals. The frequency of different type toxicities will be tabulated by each cycle of the treatment.
2. To estimate tumor response rate. The probability of tumor response (definition: section 8.1) will be estimated using binomial distribution along with 95% CI.
3. To estimate a 6-month progression-free survival rate. The 6-month progression-free survival is defined as patient who is alive and disease progression free at the time of 26-week (6 months) from first day of the treatment (definition of disease progression: section 10.0). The probability of 6-month progression-free survival will be estimated using binomial distribution.
4. Correlative study: Apoptosis can be triggered through either the intrinsic (mitochondrial) or extrinsic (receptor) pathways. The study will focus on regulators of both the intrinsic (Bcl-2, Bcl-XL, Mcl-1, Bax, Bak) and extrinsic (FLIP, survivin, XIAP) pathways. Serum will be collected for analysis of apoptotic protein levels immediately before the first dose and after one week of therapy. Every effort will be made to collect tumor tissue before and after treatment. Descriptive statistics will be used to summarize the protein expressions and patient's MGMT methylation status.

The Cox's proportional hazard model will be used to explore the association between change of the proteins and patient's survival status.

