### **11.4 Interim Monitoring**

This is a single arm, open label, single agent, and fixed dose phase II clinical trial. One planned safety assessment will be performed after the first 25 patients are accrued into the study and have had at least one cycle of the treatment. If the following pertain, the study will be suspended pending review by the ABTC DSMC: lower 95% confidence bound on the rate of toxicities grade  $\geq 3$  (this translates to dose limiting toxicity events of any type) exceeds 18%/ or if 4 or less patients ( $\leq 16\%$ ) achieved disease progression-free survival at 6 months.

Progression-free survival at 6 months has not been proven as a validated survival surrogate. The study uses PFS-6m to describe the nature process of the disease without any effective treatment, which the PFS-6m is about 15% in this patient population. A consensus decision by ABTC, CTEP, and the sponsor is required for stopping the trial earlier, if it is necessary due to any reasons.

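### For progression, the exploratory serum-biomarker analysis takes yes/no status at 26 weeks as its outcome, although the trial collects progression and death times that would carry more information

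*Protocol*

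**What the plan says.** The protocol describes the biomarker analysis in four places, which do not name the same outcomes.

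- Section 1.0, secondary objective 4, is exploratory and names overall survival only: "To explore associations of the clinical outcome (overall survival) among the changes of potential serum biomarkers, baseline tumor protein expression and gene methylation status".
- Section 2.0 (Correlative Studies Background) adds a second outcome: "We hypothesize the correlative biomarkers will predict overall survival and six month progression free survival".
- Section 9.5.2 repeats both: "Protein levels measured by ELISA will be correlated with clinical outcomes including overall survival and six month progression free survival".
- Section 11.3 item 4 gives the only association model: "The Cox's proportional hazard model will be used to explore the association between change of the proteins and patient's survival status".

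Six-month progression-free survival is defined in section 11.3 item 3 as a patient being "alive and disease progression free at the time of 26-week (6 months) from first day of the treatment", and the same item says "The probability of 6-month progression-free survival will be estimated using binomial distribution". Section 11.4 supplies the reference rate without effective treatment: "which the PFS-6m is about 15% in this patient population". It also says that this measure is not a validated surrogate for survival and is used to describe the course of the disease.

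The protocol nowhere relates the biomarkers to progression-free time.

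**The concern.** The data for a time-to-event analysis are already collected. Scans precede every odd cycle (sections 4.2 and 8.2), a neurological examination precedes every cycle (section 9.1), progression is defined (sections 8.1 and 10.0), and deaths are followed every two months (section 10.0).

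Reducing this to status at 26 weeks has three effects:

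- Failures at week 4 and at week 25 become identical.
- Events after week 26 are ignored.
- The contrast rests on a small event-free group.

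The status is also awkward to observe. With 28-day cycles the scans fall at about weeks 8, 16, 24 and 32, so none falls at week 26. A patient who stops treatment unprogressed has no further scheduled scan after the off-treatment one and may have no 26-week status at all.

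With 56 patients and eight proteins listed in section 11.3, a real association with progression is more likely to be missed on this scale than on the time scale.

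**Working it through.** **What the protocol states.** It gives no power, test, alpha or effect size for the biomarker correlation, so there is no figure to reproduce on this exact point. The nearest is the overall-survival power in section 11.2: 52 events, one-sided alpha 0.1. With power = Φ(√52 × |ln HR| − 1.2816):

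- HR 0.75: Φ(7.211 × 0.2877 − 1.2816) = Φ(0.793) = 78.6%, stated as 80%.
- HR 0.70: Φ(7.211 × 0.3567 − 1.2816) = Φ(1.290) = 90.2%, stated as 90%.

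These figures hold to within 2 points. They show that the overall-survival half of the biomarker analysis has a time-to-event outcome with about 52 planned deaths.

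**Size of the event-free group.** 56 × 0.15 = 8.4 patients, leaving 56 − 8.4 = 47.6 treated as identical failures. If the rate were 10%, 20% or 25%, the event-free count would be 5.6, 11.2 or 14.

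**Cost of the cut.** This was simulated because the protocol gives no effect. The assumptions are:

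- 56 patients with serum data and a standard normal biomarker.
- Exponential time to progression or death, with hazard multiplied by HR per SD and calibrated so that 15% (or 25%) are event-free at 26 weeks.
- Progression recorded at the next 8-week assessment, with follow-up to 104 weeks.
- A two-sided 5% likelihood-ratio test.

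The comparison is logistic regression on status at the last assessment by week 26 against a grouped-time (complementary log-log) proportional hazards model on all intervals. Ranges are over separate runs at 15%.

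| HR per SD | 26-week status | Grouped time | Difference (points) |
|---|---|---|---|
| 1.3 | 32–34% | 47–48% | 13–15 |
| 1.5 | 60% | 79–81% | 19–21 |
| 1.75 | 82–87% | 94–96% | 7–14 |

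The low end is one run at HR 1.75 (87% against 94%, which is 7 points on the rounded powers and up to about 8 before rounding). Other runs at that effect give 82% against 96%. Type I error was 4–7% for both methods.

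**Sensitivity.**

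- Rate of 25%: 32% against 49%, 62% against 81% and 85% against 97% at HR 1.3, 1.5 and 1.75, so differences of 17, 19 and 12 points.
- 4-week grid, HR 1.5: 61% against 82%.
- 10% dropout by week 26, HR 1.5: 57% against 79%.
- HR 1.3 to 2.0 per SD at 15%, also using other tests and exact times: 11 to 23 points.
- Rates of 10–25% and 50–56 patients: about 6 to 31 points.

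**Choice of time-to-event model.** On an 8-week grid many progression times tie. A Cox fit with the Breslow correction has a true size of about 1%, and its power at HR 1.5 and a 15% rate is about 52%. That is below the 60% for 26-week status, so the gain depends on using the grouped-time form.

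**The case against.** Several counter-arguments have force.

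- **The main biomarker analysis is already time-to-event.** Objective 4 names overall survival alone, and section 11.3 gives it a Cox model. A reader might infer that the whole serum hypothesis rests on about 8 event-free patients. The documents do not support that. The loss concerns only the progression outcome added in sections 2.0 and 9.5.2.
- **No binary test is prescribed.** The binomial sentence in section 11.3 item 3 concerns estimation of the rate, and the test may properly be left to a statistical analysis plan. A reader might infer that the protocol fixes a logistic or similar test, but it does not. What it does fix, by name and definition, is the outcome. The word for inclusion in section 9.5.2 leaves room for other outcomes, yet progression-free time is not mentioned anywhere.
- **The power figures come from outside the protocol.** Effect size, biomarker distribution and test are all assumed, and the data were generated under proportional hazards, which favours the recommended model. The 15% is a rate without effective treatment, not a forecast for this cohort. All of this stands, so the loss can be quoted only with its conditions.
- **The time analysis has its own weaknesses.** Patients who stop treatment unprogressed for toxicity, refusal, non-compliance or delay then have only survival follow-up, so censoring may be informative. The change in protein is known only after the week-2 sample. Both points stand and shape the fix.
- **Relating biomarkers to a declared secondary endpoint is coherent.** This is so, and it is a reason to keep the 26-week status alongside the time analysis.

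**Conclusion.** The point holds for the progression half of the exploratory serum-biomarker analysis only. There the named outcome discards timing that the trial collects and leaves about 8 event-free patients at the 15% reference rate.

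The cost is roughly 8 to 21 points of power for HR 1.3 to 1.75 per SD, under proportional hazards, exponential progression-free times, 56 evaluable patients and a two-sided 5% test. It is about 6 to 31 points over rates of 10–25% and 50–56 patients. These are conditional figures. The simulations did not include non-proportional hazards or the week-2 landmark.

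The primary survival estimate, the interim rule in section 11.4 and the decision rule in section 11.5 are not affected.

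**What to change.** In sections 9.5.2 and 11.3 item 4:

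- Add progression-free survival time (progression or death, censored at the last progression assessment) as the main progression outcome for the biomarker association.
- Analyse it with a grouped-time (complementary log-log) proportional hazards model on the assessment intervals, not with a Breslow-tie Cox fit.
- Start the clock at the first day of treatment for baseline levels. When the predictor is the change in protein level, start it at the week-2 sample and include only patients still event-free then.
- Keep 26-week status as a descriptive or supporting outcome, and leave the binomial estimate in section 11.3 item 3 as it is.
- Add a sensitivity analysis for patients who stop treatment unprogressed, since their censoring may be informative.

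At the same time, align objective 4 in section 1.0 with sections 2.0 and 9.5.2 on whether progression is a biomarker outcome.

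The cost is wording and a small number of extra model fits, with no new visits or patients. The downsides are that progression times are known only to the scan interval, that a hazard ratio is slightly less direct to read than a six-month difference, and that the censoring assumption has to be examined.
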